**Biological sample collection**

We will collect blood, stool and urine from the participants at enrolment and at the end of nutrition intervention. Overall, 5 ml of whole venous blood will be collected aseptically from each of the participants as per the SOPs. The blood biomarkers that will be tested in this study are L-carnitine, Citrulline, KT Ratio, C-reactive protein (CRP), and Alpha-1-acid glycoprotein (AGP). CRP is an acute phase protein and can be detected during infection. Increased level of AGP in serum indicates systemic tissue injury, inflammation and infection. Both Citrulline and KT Ratio indicate EED in children. Stool will be collected to investigate the concentrations of MPO, NEO and A1AT in the fecal samples. We will measure L-carnitine levels in the urine samples of each participants. All the assays will be done at icddr,b.

Laboratory Investigation

| **Investigations** | **Type of tests** |
| --- | --- |
| L carnitine in plasma and urine | Enzyme-linked immunosorbent assay (ELISA)* |
| Myeloperoxidase (MPO) | Enzyme-linked immunosorbent assay (ELISA)* |
| Neopterin (NEO) |
| Alpha-1 antitrypsin (AAT) |
| Citrulline |
| Kynurenine: Tryptophan (KT) Ratio |
| C-reactive protein (CRP) |
| Alpha-1 acid glycoprotein (AGP) |
| Serum creatinine (S. Cr) | icddr,b diagnostic laboratory |
| Potential Renal Solute Load (PRSL) |

*ELISA will be done at icddr,b laboratory

Outcome measures/variable:

Primary Outcome Variable:

1. Rate of weight gain

Secondary Outcome Variable:

1. Duration of hospital stays
2. EED biomarkers (MPO, NEO, A1AT, KT Ratio, Citrulline)

## Sample Size Calculation and Outcome (Primary and Secondary) Variable(s)

| Clearly mention your assumptions. List the power and precision desired. Describe the optimal conditions to attain the sample size. Justify the sample size that is deemed sufficient to achieve the specific aims. |
| --- |

The sample size is estimated considering the primary outcome variable. For the primary objective, we have considered the study report, done by Alp Haiden et al, where they found the mean difference between the rate of weight gain after supplementation was 2.4 (The weight was measured in kg) and the standard deviation was 4.3 (5). Setting the level of confidence at 95% (Z1-α =1.645) and 80% of power, using the below formula, the estimated sample size is 49 participants in each group with a 10% attrition rate.

The sample size is calculated based on the following formula:

The total sample size for this study will be 98 (49 in Group A, and 49 in Group B). Sample size was estimated based on the following formula:

n= 2 × (
[figure not shown]
 ) ² × S²

Herein,

n = the sample size required in each group

S = standard deviation of the primary outcome variable = 4.3

δ = size of difference of clinical importance = 2.4

δ˳= clinically acceptable margin = 0.1

Z1-α = 1.645 (at a 5% level of significance)

Z1-β = 0.845 (for 80% power)

n = 49 participant in each group with 10% attrition rate

**Investigations**

The measurement of free L-carnitine in plasma will be done in every enrolled patient. Pre-Post test will be done. Pretest will be on the first day of enrolment and posttest will be on the 15th day after completion of supplementation. Blood sample will be collected with proper aseptic procedure and SOP will be followed for blood L-carnitine level assay.

SOP for blood collection, processing and storage:

1. Blood collection site is prepared with a clean, disposable pad in a sterile fashion as to keep area contamination free.
2. Blood collection tube is prepared with appropriate label which include patient’s name, ID, date and time of collection.
3. Blood sample is collected in a race element free blood collection tube.
4. The blood tube is allowed to stand at room temperature for approximately 30 minutes.
5. After 30 minutes, tubes are centrifuged @3000 rpm for 10 minutes.
6. Plasma/serum are transferred into appropriately labeled cryo vials.
7. In a suitable time (as soon as possible) the samples are transferred to the central laboratory by maintaining cold chain.
8. Upon received in the lab, the samples are stored in the ultra-freezer (-80˚C) until analysis is complete.
9. After proving all results, samples will be discarded.

If centrifuge is not possible in the field site following steps need to be maintained for transferring whole blood to the central laboratory:

1. The blood tubes are allowed to stand at room temperature for few minutes.
2. The tubes are placed in a cool box with sample rack.
3. Sufficient Ice packs are needed to be placed inside the cool box. However it should be noted that ice pack should not touch the blood collection tube.
4. When blood collection is complete, an appropriate list for the entire specimen is prepared and this list is placed into the plastic bag. This plastic bag containing the completed specimen list is placed on top of the inner side of the lid before closing the cool box.
5. Samples are transferred to the central laboratory (icddr,b) as soon as possible (within 3-4 hours) by maintaining cold chain and if possible, temperature is monitored using thermometer.

To reduce the contamination, following things also needs to consider:

1. As much as possible, only certified trace element free supplies need to be used.
2. Powder-free gloves need be used during sample collection, preparation, storage and analysis.  Powdered gloves will contaminate sample.
3. All screening supplies, which include gauze pads, band aids, tissue paper, alcohol pads, and collection vials, need to be stored in a clean plastic box with a snap lid for storage.

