The study involves interview at the time of enrolment at NRU. Questionnaires will contain information about medical history including nature and duration of illness, medication for current illness; socio-demographic characteristics such as- age, sex, religion, parental age with education, parents occupation, monthly family income, number of siblings etc. Information will also be collected about child’s feeding practice such as- history of breast feeding, formula or other complementary feeding, immunization status and recent or past history of respiratory infections. No sensitive questions will be asked.

1. **Use of records/data**:

We will use the data collected from the enrolled patients upon ensuring confidentiality, privacy and anonymity.

1. **Use of specimens**:

We will collect biological sample (stool, urine and 5.0 ml of blood) on the enrolment day as well as after completion of 15 days of supplementation which will help us to assess carnitine level of the child and also assess the effect of L-carnitine supplementation on rate of weight gain and also on biomarkers of EED. We will store the sample for future studies at icddr,b laboratory for 5 years under the ownership of icddr,b.

1. **Use of photographs, video and audio records**:

We would not be collecting video or audio records in our study.

1. **Counseling:**

Counselling session for the mother or caregiver will be arranged in the NRU to help understanding the benefit of this study.

1. **Patient management or referral:**

All the study participants will be managed as per routine management guidelines of icddr,b. If referral is required, it will be done as per hospital guidelines.

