**Intervention**

Investigational products:

- L- carnitine oral solution (100mg/ml) for Group A
- Placebo for Group B- Oral solution identical in appearance and taste to the active preparation (L-carnitine syrup) with no therapeutic value

**Dosage:** 100 mg/kg/day, divided into 3 doses per day for 15 days.

**Packaging and labeling:** The investigational product will be dispensed in a 100ml bottle.

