**Drug accountability**

The L-carnitine syrup formulation will be provided for 15 days to study participant at nutritional rehabilitation unit (NRU) under controlled set-up. They will be evaluated by measuring the rate of weight gain at 15 days of supplementation and 180 days of completion of supplementation. A telephonic follow-up will be done on after 15 days of completion of supplementation. Study investigator will update accountability records of the investigational product according to ICH E6, GCP guideline. Investigational product will not be provided to any third party.

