**Management**

Children will be given their first dose of supplementation when they would be considered improved, i.e. no diarrhea for last 24 hours, patient fulfill the criteria of NRU transfer (presence of oedema, or/and WLZ <-3SD, or/and WAZ <-4SD). At NRU after randomization trained research staff will observe each child for 60 minutes following ingestion of investigational product and record any adverse event- nausea, vomiting etc. Vomiting is defined as the forceful emptying of stomach contents and will be recorded if it happened within 60 minutes following the administration of investigational product. Children will get supplementation of investigational product in addition to standard of care at NRU for 15 days. Supplementation will be given at every 8 hours under supervision of a trained staff.

**Study Days**Patients will be followed up every day by a study physician at NRU for 15 days. Adverse events will be documented and drug accountability recorded. During this intervention period if study participants fulfill the discharge criteria of NRU (WLZ/WHZ ≥ -2SD, WAZ ≥ -3SD and oedema resolved), we will discharge the patient with remaining dose of the syrup and advise them to come for follow up into after completion of the remaining dose. This same method will be applicable for both the intervention arm and placebo arm.

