Response: Thank you sir for your valuable opinion. Yes, we will also try to understand the distribution of baseline carnitine level.

Comment: “In terms of the secondary outcome of study of Levocarnitine’s effect on EED, the interval of 15 days may be too short to recognize an effect on certain biomarkers. Specifically, those of gut permeability may take longer to correct.”

Response: Thank you sir for your valuable guidance and suggestion. In our study design we have a plan to collect sample for EED biomarkers for reassessment at day 15, after completion of intervention. We don’t know whether 15 days or 30 days are adequate to test faecal biomarkers. There is no data on the effect of carnitine supplementation on EED biomarkers. If we wait for 30 days to collect the samples, there would be also a chance of increasing the drop out rate. Because most of the caregivers would not allow their children to stay for such a long time in hospital. It is not feasible as well to visit their homes to collect biological samples. Therefore, we will collect samples and measure EED biomarkers at the end of intervention. Since it is the first study of its kind, we would find evidence whether 15 days are adequate or not.

Comment: “Also, the degree of baseline elevation in inflammatory biomarkers (including enteric inflammation) may be dependent on the type of pathogen causing the diarrhea that led to the child’s admission. Children with secretory diarrhea will have less elevation than those with inflammatory pathogens such as Campylobacter or Shigella. Inflammatory biomarkers to these pathogens may decrease regardless of intervention as the infection clears although likely will not normalize. One way to create a more heterogenous group without expensive pathogen testing would be to exclude children with fecal RBC positivity. Although pathogens such as Campylobacter are increasingly being recognized causing non-bloody diarrhea in addition to the more classic bloody diarrhea, this may help in excluding children with the highest levels of colitis (i.e. those that would lead to fecal RBC testing being positive). Alternatively, if the budget allows, fecal pathogen testing could be arranged and only children with viral disease enrolled as it would be expected that viral pathogens change the inflammatory biomarkers to a lesser degree. Of course, co-pathogen carriage may make screening difficult.”

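### The Investigations section, read literally, takes the carnitine post-test 15 days after the last dose, while the rest of the protocol puts it at the end of supplementation

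*Protocol*

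**What the plan says.** The timing of the post-treatment sample appears in four places in the protocol.

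- **Investigations**, the section that schedules the plasma free L-carnitine assay: "Pretest will be on the first day of enrolment and posttest will be on the 15th day after completion of supplementation".
- **Biological sample collection**: "We will collect blood, stool and urine from the participants at enrolment and at the end of nutrition intervention". L-carnitine is on the list of blood markers that follows.
- **ERC Abstract Summary**, under use of specimens: stool, urine and blood are taken "on the enrolment day as well as after completion of 15 days of supplementation which will help us to assess carnitine level of the child".
- **Appendix 1**, reply to the first external reviewer, on the biomarkers of environmental enteric dysfunction (EED): "we have a plan to collect sample for EED biomarkers for reassessment at day 15, after completion of intervention". The reply considers waiting 30 days, declines because dropout would rise, and calls home sampling not feasible.

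Three other statements set the calendar.

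- The **Intervention** section gives the duration: "100 mg/kg/day, divided into 3 doses per day for 15 days". It is used here only for the count of days.
- **Drug accountability** describes the contact after treatment: "A telephonic follow-up will be done on after 15 days of completion of supplementation". The weight evaluations named there are at 15 days of supplementation and 180 days after completion.
- **Management** (Study Days) lets a child who meets the discharge criteria go home with the remaining syrup, and staff then "advise them to come for follow up into after completion of the remaining dose".

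**The concern.** The Investigations section is where the protocol specifically schedules the carnitine assay, and it leads directly into the blood collection procedure. Staff preparing a sampling schedule would naturally work from it. Its wording counts 15 days from the end of supplementation, whereas the other sections count 15 days of supplementation.

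What is at stake is the check on repletion. Assessing carnitine level is part of the stated purpose in the ERC Abstract Summary and the Background. When the external reviewer doubted that the dose would replete all children, the investigators replied that they thought it would. The pre-post carnitine measurement is the only evidence the trial would have on that question. A level drawn 15 days after the last dose does not directly measure end-of-treatment status. If weight gain or the EED biomarkers then showed no effect, a failure to raise carnitine could not be told apart from a carnitine rise that brought no benefit.

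**Working it through.** The plan gives no figure to reproduce, so the check is a day count and a side-by-side reading.

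**Inputs**

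- First dose: study day 1.
- Length of supplementation: 15 days (Intervention), so the last day is day 15.
- Interval in the Investigations sentence, read literally: 15 days after completion.
- Interval to the telephone contact: 15 days after completion (Drug accountability).
- Interval to the later weight evaluation: 180 days after completion (Drug accountability).

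**Day count**: study day of event = last day of supplementation + interval after completion.

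- Carnitine post-test, literal reading: 15 + 15 = day 30.
- Telephone contact: 15 + 15 = day 30.
- Later weight evaluation: 15 + 180 = day 195.
- Post-treatment samples under the other sections: 15 + 0 = about day 15.
- Discrepancy: 30 − 15 = 15 days, all of it off product.

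**Side by side**

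| Section | Measurement covered | Study day implied |
| --- | --- | --- |
| Investigations | Plasma free L-carnitine | About 30 |
| Biological sample collection | Blood (carnitine listed), stool, urine | About 15 |
| ERC Abstract Summary | Blood, stool and urine; carnitine named | About 15 |
| Appendix 1 reply | EED biomarkers | 15 |
| Drug accountability | Telephone contact, no sample | About 30 |

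The second and third rows contradict the first directly, because both cover carnitine. The fourth concerns the EED biomarkers only. It supports the same reading and shows that the investigators declined a wait of about that length for those samples.

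**Is there a visit for a day-30 draw?** None is described in the text. The contact at that time is by telephone, home sampling is called not feasible, and children discharged early return on finishing their remaining doses, which is about day 15. The ERC Abstract Summary and the Biological sample collection section describe two collection occasions. A separate day-30 carnitine draw would be a third that neither mentions.

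**The case against.** The strongest answer is that a comma is missing. The Appendix 1 reply uses almost the same words with the comma in place: "collect sample for EED biomarkers for reassessment at day 15, after completion of intervention". Read that way, the Investigations sentence means the 15th day, once supplementation is complete. It then agrees with every other section and with the telephone-only contact afterwards. End-line anthropometry is also fixed on the 15th day of supplementation. The intended day can therefore be recovered, and losing every carnitine post-test would require staff to follow one clause against all the rest. This is very probably what was meant. It explains the error without removing it, because the sentence is an operative sampling rule and still says something else.

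A second answer is that carnitine level is not a listed outcome. The primary outcome is rate of weight gain. The secondary outcomes are hospital stay and five EED biomarkers: myeloperoxidase, neopterin, alpha-1 antitrypsin, the kynurenine:tryptophan ratio and citrulline. That stands in full and limits the severity.

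A third is that the participant workflow figure is not available here and may show the sampling days. That also stands. The figure could confirm day 15, but the sentence would then contradict it and would still need correcting.

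A reader might go further and take the end of the nutrition intervention, in Biological sample collection, to mean the end of the stay on the rehabilitation unit. Children who recover faster would then be sampled earlier, which would bias the EED comparison. The documents do not support this:

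- The project summary, Study Design, Anthropometric measurements and Appendix 1 reply all use intervention for the 15-day supplement.
- Study Days treats early discharge as falling within the intervention period.
- The ERC Abstract Summary keeps the total at 15 days whatever the discharge date.
- No section ties sampling to discharge.

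Nor is it safe to say that discharged children have no sampling time. A return on completing the remaining doses implies about day 15.

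**Conclusion.** The Investigations sentence is wrong as written, and the point is minor. Taken literally, it moves the carnitine post-test by 15 days, from about day 15 to about day 30, to a time off product when the text provides only a telephone call. The result would be an off-treatment level or a missing sample, and the trial could not show whether carnitine rose by the end of treatment.

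The conclusion rests on counting the first dose as day 1 and on the sections available, without the workflow figure. The documents give no figure for how fast carnitine falls after stopping, so the size of any distortion in the level is unknown; only the timing discrepancy is quantified. The sample size, the primary analysis and the EED comparison are unaffected.

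**What to change.** Reword the Investigations sentence so that the carnitine post-test is taken at the end of supplementation: day 15, on completion of the 15 days. State that it uses the same draw as the other post-treatment samples described in Biological sample collection, the ERC Abstract Summary and the Appendix 1 reply. Add that, for children discharged early, the draw is made at the return visit on completing the remaining doses. Check the workflow figure for the same day.

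The cost is negligible. This is a wording change that uses collection occasions already planned, with no extra sample or visit and no change to treatment or follow-up.

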**Experimental procedure for analysis of L-carnitine**

Plasma L-carnitine will be measured using Enzyme-linked immunosorbent assay (ELISA). [Company name: BIOMATIK; Catalog Number: EKC34382]

For internal quality control Bi-Level trace elements serum toxicology control, Normal range and High range (UTAK Laboratories Inc, CA 91355, USA) are used. These control materials are used in each day at the beginning of analysis to check both accuracy and precision. For ensuring the quality of results Immunobiology, Nutrition and Toxicology Laboratory also participate in College of American Pathologists (CAP), (External Quality assurance programs). [Reference: AOAC Official Methods of Analysis (1990) 15thed. 2nd Supplement (1991) p: 81]

**Management**

Children will be given their first dose of supplementation when they would be considered improved, i.e. no diarrhea for last 24 hours, patient fulfill the criteria of NRU transfer (presence of oedema, or/and WLZ <-3SD, or/and WAZ <-4SD). At NRU after randomization trained research staff will observe each child for 60 minutes following ingestion of investigational product and record any adverse event- nausea, vomiting etc. Vomiting is defined as the forceful emptying of stomach contents and will be recorded if it happened within 60 minutes following the administration of investigational product. Children will get supplementation of investigational product in addition to standard of care at NRU for 15 days. Supplementation will be given at every 8 hours under supervision of a trained staff.

**Study Days**Patients will be followed up every day by a study physician at NRU for 15 days. Adverse events will be documented and drug accountability recorded. During this intervention period if study participants fulfill the discharge criteria of NRU (WLZ/WHZ ≥ -2SD, WAZ ≥ -3SD and oedema resolved), we will discharge the patient with remaining dose of the syrup and advise them to come for follow up into after completion of the remaining dose. This same method will be applicable for both the intervention arm and placebo arm.

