**Safety Plan**

Gastrointestinal symptoms (Nausea, Vomiting, Diarrhea and Fever) are the most likely adverse event. The safety population will include all subjects who received at least one dose of the investigational products under study. Descriptive statistics will be used to summarize adverse events, safety results, and demographic variables. Reasons for dropouts and timing will be documented. Any dosing errors will be described, with any adverse events resulting.

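### Vomiting is made recordable only by reference to the 60 minutes after a dose, which conflicts with the unrestricted daily adverse-event documentation, and no collection is described for home doses

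*Protocol*

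**What the plan says.** - **Expected events.** The Safety Plan states: "Gastrointestinal symptoms (Nausea, Vomiting, Diarrhea and Fever) are the most likely adverse event". The ERC Abstract Summary, under potential risks, also lists vomiting.
- **Post-dose observation.** Under Management, at the Nutritional Rehabilitation Unit (NRU), "trained research staff will observe each child for 60 minutes following ingestion of investigational product and record any adverse event- nausea, vomiting etc".
- **The vomiting sentence.** The next sentence defines vomiting and says it "will be recorded if it happened within 60 minutes following the administration of investigational product". No other symptom is given a time limit.
- **Dosing schedule.** The Intervention section has the product "divided into 3 doses per day for 15 days". Management adds: "Supplementation will be given at every 8 hours under supervision of a trained staff".
- **Daily follow-up.** The Study Days paragraph, directly after the vomiting rule, says: "Patients will be followed up every day by a study physician at NRU for 15 days". It continues: "Adverse events will be documented and drug accountability recorded". Neither sentence carries a time window.
- **Early discharge.** If a child meets the NRU discharge criteria during the 15 days, "we will discharge the patient with remaining dose of the syrup", and the family is asked to return once the doses are finished. Drug accountability adds a telephone contact after supplementation ends, without saying what is asked.
- **Safety analysis.** The Safety Plan includes everyone who took at least one dose and plans descriptive summaries of adverse events.

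**The concern.** A one-hour window suits the question of whether a dose was kept down. It is a poor event definition for an oral product given every 8 hours, because vomiting in hours 2 to 8 after a dose falls outside it. Staff also have two instructions side by side: a specific one that ties vomiting to the first hour, and a general one that documents adverse events at daily follow-up. Different recorders could follow different instructions, and the vomiting counts would then mix two definitions.

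Doses taken at home raise a second, separate issue. Observation and daily follow-up are both described as taking place at the NRU. Once a child leaves, the text says nothing about how adverse events are collected while the remaining doses are taken. Duration of hospital stay is a secondary outcome that the trial hopes to change, so time under observation need not be equal in the two arms. What is at stake is the accuracy of the vomiting counts and, conditionally, their comparability between arms.

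**Working it through.** The protocol gives no figure for hours of adverse-event observation, so there is none to reproduce. The inputs are the 60-minute window (Management), three doses a day for 15 days (Intervention), and 8-hourly dosing (Management).

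**1. Width of the vomiting window on the ward**

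- Per day: 3 doses x 60 min = 180 min; 180 / 1,440 = 12.5%, or 3 of 24 hours.
- Over a full 15 days as an inpatient: 15 x 3 = 45 doses, so 45 of 15 x 24 = 360 hours.

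Doses 8 hours apart do not give overlapping windows, so 3 hours a day is the maximum.

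**2. What could be missed**

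The documents give no timing of vomiting, so only a range under assumptions is possible. Both lines assume that the vomiting sentence is applied as written and that later episodes are not picked up at the daily physician follow-up.

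- Episodes spread evenly over the day: 1 - 0.125 = 87.5% unrecorded, or 7 of 8.
- Half of episodes within an hour of a dose: half unrecorded.

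If later episodes are documented at the daily follow-up, the loss on the ward could be nil.

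**3. Early discharge**

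The protocol gives no discharge days or share of children discharged early. For assumed discharge at the end of day d, window hours = 3d and home doses = 3 x (15 - d):

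| Assumed discharge day | Vomiting-window hours, of 360 | Share | Home doses, of 45 |
|---|---|---|---|
| 5 | 15 | 4.2% | 30 |
| 8 | 24 | 6.7% | 21 |
| 10 | 30 | 8.3% | 15 |
| 12 | 36 | 10.0% | 9 |
| 15 | 45 | 12.5% | 0 |

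**4. Possible difference between arms**

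Take, for illustration only, one arm discharged on day 10 and the other on day 12, with the same constant true event rate and nothing collected at home. The ratio of observed time is 30 / 36 = 0.83, so the arm that leaves earlier would show about 17% fewer events. The ratio is the same (10 / 12) if ward events are counted around the clock, so correcting the vomiting sentence alone does not remove it. If both arms leave at the same time, or if home events are fully collected, this difference disappears.

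**5. Which events the limit reaches**

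The 60-minute condition sits in a sentence about vomiting. Nausea, diarrhoea and fever fall under the Study Days documentation, which has no window. Serious events are notified to the ethics committee under Ethical Assurance for Protection of Human rights, also with no window.

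**The case against.** The best defence is that the 60-minute sentence only describes the task of the staff who watch the child after each dose. It does not contain the word only, and it does not say that later vomiting is excluded. The daily physician follow-up can document later episodes. A fixed window also gives a standardised, directly observed count of dose-related vomiting, and under double blinding it is the same in both arms. On that view two neighbouring sentences need tidying and nothing more.

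Much of this stands. On the ward, the window by itself under-counts equally and does not bias the comparison. The lenient reading of the sentence is possible. What it does not remove is the conflict: the specific sentence attaches a time condition to recording vomiting, and a recorder who follows it will leave out later episodes.

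On home doses, the defence is that children return after finishing the syrup, that a telephone contact is planned, and that the questionnaires listed as Appendix 3 were not available for this review. A form may already ask about symptoms at home. That stands too, so the point is limited to what the visible text describes.

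Two stronger readings are tempting. A reader might infer that the whole safety comparison sees no more than 3 of 24 hours; the text does not support this, because the limit concerns vomiting alone. A reader might also infer a safety bias in favour of L-carnitine. That would need a shorter stay in the active arm, enough discharges before day 15, and no collection of home events. The documents establish none of these.

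**Conclusion.** The point holds in a limited form. The vomiting sentence and the daily documentation sentence under Management conflict. Applied as written, the first confines the recording of one expected adverse event to at most 3 of 24 hours a day on the ward and under-counts it in both arms. The shortfall ranges from nil, if daily follow-up captures later episodes, to 7 in 8, if it does not and vomiting is spread evenly over the day. The documents do not allow a narrower range.

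For doses taken at home after early discharge, no visible section describes adverse-event collection. Observation time could therefore differ by arm if length of stay differs. The size and direction are unknown: a shorter stay in the active arm would lower its count, and a longer stay would do the opposite. The planned safety analysis is descriptive, so no formal test is affected. The change is still worth making, because the counts will be read side by side and it is cheap.

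**What to change.** 1. Reconcile the two sentences under Management. Have every vomiting episode recorded per 24 hours at the existing daily physician visit, and flag those within 60 minutes of a dose. The dose-related count is kept as a subset.
2. For children discharged early, state that vomiting, diarrhoea and fever since discharge are collected by caregiver recall at the existing end-of-supplementation visit. If the questionnaire already does this, a cross-reference is enough.
3. Summarise events together with the observed child-days in each arm, separating ward days from recalled days at home, so that unequal observation time is visible.

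The cost is about one line on the daily form and one on the return-visit form, with no new visits or staff. The downside is small: recall after discharge is less accurate than observation on the ward. The change concerns data capture only and alters nothing in treatment or discharge.
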